#### Depression, Anxiety, and Stress

Data will be gathered from the respondents about their mental and well-being. We will use the Depression, Anxiety, and Stress Scale (DASS). The DASS is a set of three self-report scales designed to measure the negative emotional states of depression, anxiety, and stress. Each of the three DASS scales contains 14 items, divided into subscales of 2-5 items with similar content [22].

#### Well-Being

The Short Warwick Edinburgh Mental Well-Being Scale is a shortened version of the Warwick-Edinburgh Mental Well-Being Scale. It measures both mental and emotional well-being (how “good” somebody feels) and psychological functioning (how well somebody thinks they are functioning). This scale is suitable for ages 13-74 years and works well as a “before” and “after” tool to measure the change in well-being during an intervention or specific program [23].

#### Sources of Health Information, Social Media, Technology Access, and Familiarity

Information will be gathered about cell phone ownership in households, type of cell phone, access to the internet, and knowledge of SMS text messaging [24,25].

#### Perceived Access to Health Care

Information will be collected from the respondents regarding access to health care. We will use the Perceived Access to Health Care questionnaire. The questionnaire includes six dimensions: (1) availability, (2) accessibility, (3) affordability, (4) accommodation, (5) acceptability, and (6) awareness. In addition, the psychometric evaluation was conducted on the instrument’s initial version with 31 items on a 5-point Likert scale (strongly agree to strongly disagree) [26].

#### Health Literacy

Rapid Estimate of Adult Literacy in Medicine will be used to assess the health literacy of the study participants. It is a quick screening tool to assist physicians in identifying patients with limited reading skills and in estimating patient reading levels. “At risk patients” are defined as those with a score of six or less [27].

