### Study Intervention

The HEAL intervention will be designed based on the SMAART model to enhance healthy eating and active living for the individuals participating in the study. This intervention will ensure the coordination of social, economic, and health-related parameters to enhance the health and well-being status of the population. The SMAART model works on the principles of data, information, and knowledge; human-centered approach; information processing theory; and humanistic, behavioral, and learning theories [17]. The intervention stage will have two parallel groups (case and control) for comparison. Individuals in the intervention group will be provided access to the informatics-based intervention for enhancing their healthy eating and active living. The participants from the intervention stage will be included in the study based on participants from the baseline stage consenting to participate in the intervention. The participants will be assigned to the intervention or control group through randomization. They would be provided information on good dietary habits and the importance of regular physical exercise for maintaining good health and well-being. Individuals in the control group will be provided an educational booklet as standard care. The intervention will be a tailored multilingual digital health intervention. Both the groups will undergo a series of baseline and follow-up assessments for estimation of change in eating patterns, physical activity, and well-being to assess the impact of intervention. The study location includes both the urban and rural areas of selected sites, and the study duration is 3 years. The study population includes all adults aged 18 years and older. The inclusion criteria are (1) individuals aged 18 years and older, (2) individuals from both urban and rural areas, and (3) individuals who consent to participate in the study.

Efforts will be made to include individuals of varied age groups, gender, location, and socioeconomic status. The exclusion criteria consist of (1) individuals younger than 18 years of age, (2) individuals who would not give their consent, and (3) individuals who have impaired cognition.

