### Ethical Considerations

This study (protocol PMCHRI-IHEC-067) gained approval from the Panimalar Medical College Hospital and Research Institute Institutional Human Ethics Committee (Central Drugs Standard Control Organization Registration ECR/1399/Inst/TN/2020) in March 2022, with approval PMCH&RI/IHEC/2021/078 dated March 15, 2022. The study will be conducted according to the Declaration of Helsinki, as it involves human participants [18].

The institutional review board–approved informed consent form will be administered by the research team to the eligible individuals for the study. The research team will describe the study, time required, and benefits of the study results to the participants, and those willing to participate and give their consent will be enrolled in the study. Written informed consent will be obtained in both English and local Indian dialects at the time of data collection if the participants are able to read and understand the questionnaire. In the case of participants without formal education, an audio recording of the consent will be done. Study participants will be allowed to withdraw from the study at any time [19]. No compensation will be provided.

Data security will be ensured through regular backups in password-protected computers in the locked office of the principal investigator. Data will be stored for 5 years from the point of study completion, after which it will be destroyed. All the physical data files will be stored in a locked file cabinet in the office. The information will be accessible to members of the research team only.

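### The well-being scale's stated age range ends at 74 although enrolment has no upper age limit, and a reading test measures health literacy in a cohort that admits people who may not read

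*Protocol article*

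**What the plan says.** **Well-being.** The Well-Being section says of the short Warwick-Edinburgh scale: "This scale is suitable for ages 13-74 years". The Study Intervention section sets eligibility: "The study population includes all adults aged 18 years and older". Its exclusions are age under 18, refusal of consent, and "individuals who have impaired cognition". None of them caps age. The same section says both groups are assessed repeatedly for "estimation of change in eating patterns, physical activity, and well-being to assess the impact of intervention", so well-being is one of three named measures of change.

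**Health literacy.** The Health Literacy section states: "Rapid Estimate of Adult Literacy in Medicine will be used to assess the health literacy of the study participants". It describes the instrument in terms of reading: "It is a quick screening tool to assist physicians in identifying patients with limited reading skills and in estimating patient reading levels". A score of six or less is classed as at risk.

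**Who may be unable to read.** Under Ethical Considerations, written consent is taken "if the participants are able to read and understand the questionnaire". For others there is a separate route: "In the case of participants without formal education, an audio recording of the consent will be done". Inability to read is not an exclusion.

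**Related items.** Educational status is among the data listed under Sociodemographic Characteristics. Data Analysis plans a multivariate regression for the determinants of inequity and does not list the model's variables. The Results section says that baseline recruitment has not yet begun.

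**The concern.** The two instruments raise different problems.

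For well-being, the article states the ages for which the scale is suitable and then enrols people beyond them. Anyone aged 75 or over would contribute a score that the article's own description does not support, on a measure used to judge the intervention.

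For health literacy, a reading score stands in for the wider construct. Among people who read, a low score carries information. A person who cannot read can only return the lowest score, whatever that person knows about health. Two things are then at stake:

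- The reported share at risk would mix non-readers with poor-scoring readers.
- An association between health literacy and education would arise partly because both reflect schooling. It could be reported as a finding about inequity and used to shape the intervention, which the article says the baseline findings will guide.

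**Working it through.** The article gives no figure to reproduce on this point. The check sets its statements side by side, followed by a sense of scale.

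**Step 1: age.**
- Range of the scale (Well-Being): 13 to 74.
- Range enrolled (Study Intervention): 18 with no upper limit.
- Overlap: 18 to 74. Eligible but outside the scale's range: 75 and over.
- The article also says efforts will be made to include varied age groups, so older adults are not incidental.

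**Step 2: reading.**
- Who is tested (Health Literacy): the study participants, with no subgroup exempted.
- What is tested: reading skill and reading level.
- Who may not read (Ethical Considerations): written consent depends on reading ability, and an audio route exists for those without formal education. That non-readers will be enrolled is an inference from these two statements. Nothing in the exclusions prevents it.
- Consequence: a person who reads none of the test gets the lowest score, which lies within the at-risk band of six or less.

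**Step 3: effect on the reported proportion.** Let *p* be the share who cannot read and *q* the share of readers scoring six or less. Then

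share at risk = *p* + (1 − *p*) × *q*

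The first term is fixed by the instrument. Even with *q* = 0 the share at risk is *p*. Unless non-readers are recorded separately, *p* and *q* cannot be recovered from the reported total. If *p* is higher among people with less schooling, as the consent procedure itself implies, the first term alone produces an association with education.

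**Step 4: scale.** The only input from the article is the recruitment target of 6350. The shares are assumptions.

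| Assumed share | Calculation | People |
|---|---|---|
| 10% cannot read | 6350 × 0.10 | 635 |
| 30% cannot read | 6350 × 0.30 | 1905 |
| 1% over 74 | 6350 × 0.01 = 63.5 | about 64 |
| 5% over 74 | 6350 × 0.05 = 317.5 | about 318 |

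The last two rows apply to baseline only. The intervention stage takes only those baseline participants who consent to it, so 6350 is too large a base for the change in well-being. The numbers there would be lower by an amount the article does not allow one to compute.

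**The case against.** **The reading test does what it is said to do.** By the article's description, the tool exists to pick out people with limited reading skills, and flagging a non-reader is its intended result. A reader might infer that the article contradicts itself here. It does not. What stands is narrower: the tool's output is used as the measure of health literacy for everyone, and for non-readers it carries no information on that construct beyond reading.

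**Non-readers are not expressly mentioned.** This is correct. Lack of formal education is not the same as inability to read. The inference remains fair, because written consent is made conditional on reading.

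**The regression is not specified.** A reader might infer that health literacy and education enter one model and that their effects cannot be separated. The article supports neither step. It does not list the model's variables, and readers can still vary in reading score at a given level of schooling. What stands is that an association between the two is partly built in, in whatever analysis relates them.

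**The age mismatch may be small and balanced.** Assignment is randomised, so people aged 75 and over should fall in both groups. No bias in the comparison has been shown. The mismatch remains a question of whether those scores are valid, and the article does not address it.

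**Such details belong in a study manual.** The article refers to one, and coding rules may be there. The age conflict, however, and the choice of a reading test for all participants are stated in the article itself.

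**Conclusion.** The point holds in two parts.

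1. The stated age range of the well-being scale does not cover everyone who may be enrolled, and the scale serves a measure used to assess the intervention. The two sections must be reconciled. This part rests directly on the text.
2. The health-literacy measure cannot separate inability to read from low health literacy, and its association with schooling is partly built in. This part rests on the inference that some participants will not be able to read.

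The size is unknown. The counts in the table illustrate assumed shares and are not estimates, and the conclusion does not depend on them. Neither part invalidates the study. This is an inexpensive improvement with a short window: once data are collected without a marker for inability to read, floor scores cannot be sorted afterwards.

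**What to change.** Before recruitment starts:

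- **Health literacy.** Record inability to read as its own category, separate from a score of six or less. Report the share at risk and its association with education both with and without that category. Do not interpret a non-reader's floor score as a measure of health understanding. The category can always be merged back, so nothing is lost.
- **Well-being.** Keep all randomised participants in the main comparison. Pre-specify a supporting analysis in ages 18-74 and describe those aged 75 and over separately. Add a sentence reconciling the scale's stated range with the open upper age.

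The cost is one extra field on the form and a few extra analyses. Stronger steps are possible: replacing the instrument, fitting the literacy analysis in readers only, or dropping those aged 75 and over. They carry real costs. A replacement would lose comparability with studies that use the reading test, and the article does not show that a suitable local-language questionnaire exists. A readers-only analysis would leave out a disadvantaged group in a study of inequity. An age restriction in the main analysis would discard randomised participants. The point does not require any of them.

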#### Satisfaction With Health System

The Patient Satisfaction Questionnaire yields separate scores for each of seven different subscales: general satisfaction (2 items), technical quality (4 items), interpersonal manner (2 items), communication (2 items), financial aspects (2 items), time spent with the doctor (2 items), and accessibility and convenience (4 items). This questionnaire will be used both at baseline and postintervention [28,29].

### Outcomes

The study outcomes include the identification of determinants of social, economic, and health inequity. The research would further help in identifying the key areas that need to be addressed through intervention to improve the health and well-being status of the general population. Additionally, the study would also help in developing tailored interventions targeted to reduce social, economic, and health inequities.

### Data Analysis

Descriptive analysis will be conducted to report the mean and SD of the continuous variables and frequency analysis of the categorical variables. A 1-tailed *t* test will be performed to compare means between the continuous variables and a categorical dependent variable while a chi-square analysis will be performed for the categorical variables. Multivariate regression analysis will be performed to determine the determinants of social, economic, and health inequity. All analysis will be performed using SAS (version 9.1; SAS Institute Inc), and reporting of the results will be done at 95% CI and *P*<.05.

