**Methods:**

A prospective, 3-year cohort study will be conducted. This study aims to recruit 6350 individuals across rural and urban settings of Chennai. A total of 11 sites have been selected for participation in the study. Data on sociodemographic characteristics; economic inequity; HEAL profile; depression, anxiety, and stress; well-being; sources of health information; perceived access to health care; health literacy; navigation of health literacy; and satisfaction with the health system will be gathered. This study would help to explore the determinants of social, economic, and health inequity across multiple sites. SAS (version 9.3; SAS Institute Inc) will be used for data analysis, and results will be reported as 95% CI and *P* values. This study’s findings will guide the design and development of a tailored, human-centered digital health intervention to enhance the health and well-being of Chennai’s population groups.

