### Study Objectives

This study aims (1) to identify determinants of social, economic, and health inequity to enhance healthy eating and active living among rural and urban population groups of Chennai, Tamil Nadu; (2) to design and develop a digital health intervention HEAL using the SMAART (Sustainable, Multi-Sector, Accessible, Affordable, Reimbursable, Tailored) model, targeted to enhance healthy eating and active living among rural and urban population groups of Chennai, Tamil Nadu; and (3) to evaluate impact of the proposed intervention to address burden of social, economic, and health inequity to enhance healthy eating and active living among rural and urban population groups of Chennai, Tamil Nadu.

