#### Economic Inequity

The wealth index is a division of households into 5 wealth quintiles to show the relationship between wealth, population, and health indicators [20].

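### The plan fixes a one-tailed t test at P<.05 with no stated direction, which does not match the 95% confidence intervals reported with it

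*Protocol article*

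**What the plan says.** The Data Analysis section of the protocol article makes three choices that bear on this point.

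- For means: "A 1-tailed *t* test will be performed to compare means between the continuous variables and a categorical dependent variable".
- For categorical variables: "a chi-square analysis will be performed for the categorical variables".
- For all results: "reporting of the results will be done at 95% CI and *P*<.05". The Methods paragraph of the abstract makes the same pairing: "results will be reported as 95% CI and *P* values".

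On direction, the Outcomes section says: "The study outcomes include the identification of determinants of social, economic, and health inequity". For the intervention stage, Study Objectives says the aim is "to evaluate impact of the proposed intervention to address burden of social, economic, and health inequity", and Study Intervention says: "Both the groups will undergo a series of baseline and follow-up assessments for estimation of change in eating patterns, physical activity, and well-being". None of these states a directional hypothesis. The article gives no reason for using one tail and mentions no one-sided confidence bound.

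**The concern.** A one-tailed test at .05 keeps its 5% error rate only if the direction is named before the data are seen. A search for determinants has no natural single direction. Candidate variables such as age, household size or well-being score could be related to inequity either way. If no direction is fixed, the analyst may test whichever tail the data favour, and the error rate rises.

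The test also does not correspond to the interval reported beside it. A reader who is given a P value and a 95% CI for the same difference expects the two to agree on whether zero is excluded. Under this rule they can disagree, in either of two ways. If a direction is fixed, an effect on the other side cannot be declared significant, however large it is.

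Finally, the chi-square test has no direction. At the same .05, a continuous variable with an effect in the tested direction passes on weaker evidence than a categorical one.

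**Working it through.** **Inputs.** From Data Analysis: a one-tailed t test, P<.05, 95% CI. Assumption: the 95% CI is the usual two-sided interval. The planned 6350 participants (Study Design and Population) serve only to show that t and normal cut-offs coincide. With 6350 − 2 = 6348 degrees of freedom, the t cut-offs are 1.645 (one-tailed .05) and 1.960 (two-tailed .05), the same as the normal values to three decimals.

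**The plan's own figure.** The nominal 5% is reproduced if the direction is fixed in advance: P(Z > 1.645) = 0.050.

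**If the tail follows the data.** P(|Z| > 1.645) = 2 × 0.050 = 0.100. This is the upper bound.

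**Simulation check.** In 20,000 null t tests with 200 per group, the rejection rates were 0.050 (fixed direction), 0.100 (tail chosen from the data) and 0.052 (two-tailed).

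**Where P value and interval disagree.** The 95% CI excludes zero when |z| > 1.960. The one-tailed test rejects when z > 1.645 in the tested direction.

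| Statistic (tested direction positive) | One-tailed P<.05? | 95% CI excludes zero? |
|---|---|---|
| z > 1.960 | yes | yes |
| 1.645 < z < 1.960 | yes | **no** |
| −1.960 < z < 1.645 | no | no |
| z < −1.960 | no | **yes** |

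**Example.** z = 1.80 gives one-tailed P = 0.036 and two-tailed P = 0.072. The 95% CI is 1.80 ± 1.96, or −0.16 to 3.76 standard errors. The result would be reported as significant with an interval that includes zero.

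**How often, with no true effect.**
- Fixed direction, significant but CI includes zero: 0.975 − 0.950 = 0.025.
- Fixed direction, not significant but CI excludes zero on the other side: 1 − 0.975 = 0.025.
- Tail chosen from the data, significant but CI includes zero: 2 × 0.025 = 0.050.

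**How often, with a true effect.** The first kind of disagreement is most frequent when the true effect is about 1.8 standard errors in the tested direction: Φ(1.960 − 1.8) − Φ(1.645 − 1.8) = 0.125, or 12.5% of such tests.

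**After the change.** With a two-sided test at .05 the cut-off is 1.960. The false-positive rate is 0.050 whichever direction is observed, and P<.05 occurs exactly when the 95% CI excludes zero. If one tail were kept, one-tailed .05 would match a 90% CI, and one-tailed .025 would match the 95% CI.

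**The case against.** The strongest defence is that the t test is not where the study's conclusions come from. The same section assigns the determinants to multivariate regression, and nothing says that the t test selects variables for that model or drives a decision. Readers can also recover two-sided significance from the interval. This stands, and it limits how serious the point is.

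A second defence is that directions may be listed in the full protocol or analysis plan, which are not shown. That is possible, and the rate would then be 5%. It would not remove the mismatch with the two-sided 95% CI or with the chi-square test, because the article itself fixes the tail, the threshold and the interval. A one-sided 95% bound would agree with the test, but the article mentions none.

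Four stronger readings are tempting, and the document does not support them.

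- A reader might infer that the false-positive rate is 10%. Nothing says that the tail will follow the data, so 10% is only an upper bound.
- A reader might infer that the P values and intervals always conflict. They do so only in the two ranges shown above.
- The Economic Inequity section says "The wealth index is a division of households into 5 wealth quintiles", and a reader might conclude that a two-sample test is being misapplied to five groups. The article never says that wealth quintile is a grouping variable for the t test, and it plans no pairwise tests. Inflation from such tests would in any case be largely multiplicity, not a result of using one tail.
- A reader might infer that harm from the intervention would go undetected. The Data Analysis section does not name the comparison of intervention with control, so this assumes a use of the test that is not stated.

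**Conclusion.** The point holds. The article fixes a one-tailed .05 test with no stated direction beside 95% CIs, and the cut-offs differ (1.645 against 1.960). Followed as written, the rule can give P<.05 with an interval that includes zero, can miss an effect in the untested direction, and judges continuous and categorical variables by different standards.

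The size is modest. With no true effect and a fixed direction, each kind of disagreement occurs in 2.5% of tests. The first kind reaches at most 12.5% when a true effect lies near 1.8 standard errors. The false-positive rate is between 5% and 10%, depending on whether the direction is fixed beforehand.

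These figures assume large-sample cut-offs and the usual two-sided 95% CI. The rule should be corrected. It does not invalidate the study, because the t test is an unadjusted comparison and the determinants are assigned to regression.

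**What to change.** In Data Analysis, replace the one-tailed specification with a two-sided one and add a sentence such as: *All tests will be two-sided at the 5% level, matching the reported 95% confidence intervals.* This also puts the t test on the same footing as the chi-square test.

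The cost is one sentence and no extra data. A t-test P value doubles when the effect lies in the favoured direction, so results between 1.645 and 1.960 no longer count as significant and some power in that direction is lost. The article shows no power calculation tied to the one-tailed test, so no stated figure there needs recomputing.

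The Results section reports that recruitment had not begun as of December 2024. If that is still so, the change can be made before any data exist. Made later, a change of sidedness could look driven by the results.

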## Introduction

### Background and Rationale

The World Health Organization (WHO) identifies health inequities as “systematic differences in the health status of different population groups” [1]. Further, the WHO refers to health as “a state of complete physical, mental, and social well-being and not merely the absence of disease or infirmity” [2]. Consequently, research on health inequity is a central agenda component of the 2030 Sustainable Development Goals and various government and development dialogues [3,4]. Despite this, the WHO reports that health inequalities exist at varying degrees around the world, both within and between countries [5]. These inequalities further exacerbate health disparities between high-income and low-income, urban and rural, employed and unemployed populations, as well as between low-, middle-, and high-income countries [6] due to socioeconomic factors such as social status or income levels [7].

According to the Centers for Disease Control and Prevention, health equity can be attained when every individual can “attain his or her full health potential” and no one is “disadvantaged from achieving this potential because of social position or other socially determined circumstances” [8]. This also emphasizes the significance of measuring health inequity, promoting opportunities and monitoring the progress in health and intersectoral strategies. Additionally, measuring the interrelationship between health and its social determinants is vital to promoting effective interventions for health equity [9].

Inequalities are unfair, affect everyone, and are avoidable; however, the underlying factors causing inequality are imperfectly understood, and evidence on the effectiveness of interventions to reduce inequalities is limited [10]. Prior research has further highlighted the issue of good health for socioeconomically vulnerable groups and the need for targeted public health interventions in India [11]. A study indicated that health inequity in India is favored toward high-income populations and that despite services being available to people, there was a lack of awareness around it, especially in the rural region [12]. Considering the diversity in India and the prevalent social inequalities, the literature also emphasizes on the importance of research on health inequalities for monitoring health policies and programs [11].

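### The t test for comparing means is fixed as 1-tailed at P<.05 with no direction stated, so it either carries a 10% type I error or cannot declare a reversed effect, and its P values can contradict the 95% CIs

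*Protocol article*

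**What the plan says.** The Data Analysis section of the protocol article names one test for comparing means: "A 1-tailed *t* test will be performed to compare means between the continuous variables and a categorical dependent variable". The same sentence adds that "a chi-square analysis will be performed for the categorical variables", and the section ends with the rule that "reporting of the results will be done at 95% CI and *P*<.05". The abstract likewise says that "results will be reported as 95% CI and *P* values".

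No section names the direction to be tested or gives a reason for testing in one tail. The first study objective is "to identify determinants of social, economic, and health inequity", and the abstract says: "This study would help to explore the determinants of social, economic, and health inequity across multiple sites". For the randomized stage, the Study Intervention section describes "follow-up assessments for estimation of change in eating patterns, physical activity, and well-being to assess the impact of intervention", which is neutral as to sign.

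Between the t test and the reporting rule, the Data Analysis section also assigns the identification of determinants to a multivariate regression. It does not call that regression one-tailed.

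**The concern.** A one-tailed test needs a direction fixed in advance and a reason why the other direction does not matter. The article gives neither. Its own rationale says that "the underlying factors causing inequality are imperfectly understood", which is an argument for looking in both directions. The grouping variable is called dependent, which makes an intended direction harder still to infer.

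This is a choice that the article states, not a detail left to another document. What is at stake depends on how the gap is filled:

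- If the analyst lets the data choose the tail, each t test is twice as permissive as its nominal 5%.
- If a tail is fixed, a group difference of the unexpected sign is reported as not significant however large it is.
- In both cases, a P value and the 95% CI printed beside it can lead to different conclusions.

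The chi-square test in the same sentence is non-directional in its usual form. Continuous and categorical variables would then be judged by different standards at the same P<.05.

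**Working it through.** **Inputs.** From the Data Analysis section: a 1-tailed t test, threshold P<.05, 95% CI. The interval is not described further, so it is taken as the conventional two-sided one (assumption). The article derives no power or effect size, so there is no figure of its own to reproduce. The critical values below are for large samples. The t values are close: 1.661 and 1.984 at 50 per group, 1.649 and 1.966 at 200 per group.

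**1. Critical values.** One-tailed 5%: z(0.95) = 1.645. Two-sided 95% CI: z(0.975) = 1.960. The interval that matches a one-tailed 5% test has level 1 − 2 × 0.05 = 90%, not 95%.

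**2. Type I error.**
- Tail chosen after seeing the difference: P(|Z| > 1.645) = 2 × 0.05 = 0.10. The result is 0.10 at 50, 200, 1000 and 3175 per group, and a simulation of 1,000,000 null t statistics (198 degrees of freedom) gave 0.0996.
- Tail fixed in advance: P(Z > 1.645) = 0.05, as stated. A statistic in the other direction then has a one-tailed P above .5 and can never reach P<.05.

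These are alternatives. One test cannot suffer from both.

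**3. Disagreement between P and CI, no true effect.**
- Fixed tail, P<.05 but the CI covers zero: P(1.645 < Z < 1.960) = 0.05 − 0.025 = 0.025.
- Fixed tail, CI excludes zero on the other side but P is not significant: P(Z < −1.960) = 0.025. Together with the line above, 5% of null comparisons disagree.
- Tail chosen afterwards, P<.05 but the CI covers zero: 2 × 0.025 = 0.05.

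**4. Disagreement with a true effect in the tested direction.** With expected statistic m, the probability of P<.05 with a CI covering zero is Φ(1.960 − m) − Φ(1.645 − m).

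| m | Probability |
|---|---|
| 1 | 0.091 |
| 1.8 | 0.125 |
| 2.8 | 0.076 |
| 4 | 0.011 |
| 5 | 0.001 |

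The conflict is largest for m of about 1.8 and nearly disappears for clear effects.

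**5. Price of two-sided testing.** Where the one-tailed test has 80% power, m = 1.645 + 0.842 = 2.487. Two-sided power is then Φ(2.487 − 1.960) = Φ(0.527) = 0.70. The ratio of differences detectable at 80% power is (1.960 + 0.842) / (1.645 + 0.842) = 2.802 / 2.487 = 1.127, a rise of about 13%. Neither figure depends on the sample size, provided that the normal approximation is adequate.

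**The case against.** The strongest reply concerns reach. Several larger conclusions are tempting, and the article does not support them.

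- A reader might infer that factors will be declared determinants at half the stated strictness. They will not on this account: that task is given to the multivariate regression, and nothing makes it one-tailed. The t test is a bivariate step beside it. This objection stands.
- A reader might take it as settled that HEAL will be judged against control by this test. The Data Analysis section does not mention the randomized groups, and an allocated arm is not a dependent variable. Use of the t test there is plausible, since no other test of means is named, but it is an inference.
- A reader might split the 6350 participants into 3175 per arm and calculate how surely a harmful effect would be missed. The 6350 is the recruitment target for the cohort, and only baseline participants who consent to the intervention stage are randomized. So 3175 per arm is an upper limit.
- A reader might say that P values and CIs will contradict each other. They can, for borderline or opposite-direction results, and only if the CIs are two-sided.

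It can also be said that the article hints at directions. The Background reports that inequity in India favours people with high incomes, and the intervention is meant to improve eating and activity. That makes a tail chosen after the data the less natural reading, and so weakens the case for the 10% figure. It does not state a tested direction for any comparison, and a fixed tail brings the other defect instead. An expected benefit is also no reason to be unable to declare worsening.

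**Conclusion.** The concern holds for the t tests. A one-tailed test at 5% with no stated or justified direction has one of two defects: a type I error of 10% if the tail follows the data, or an error of 5% with no ability to declare an opposite effect if the tail is fixed in advance. The second would include worsening under HEAL, if the t test is used for that comparison.

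Assuming two-sided 95% CIs, P<.05 can stand beside an interval that covers zero. The rate is 2.5% of null comparisons (fixed tail) or 5% (tail chosen afterwards), about 12.5% at an expected z near 1.8, and about 1% or less once the expected z is 4 or more.

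The chi-square tests and the regression are not affected. The arithmetic needs no sample size beyond one large enough for the normal approximation.

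**What to change.** In the Data Analysis section, replace the 1-tailed t test with a 2-sided t test. Add that all tests, including any comparison of HEAL with control, are two-sided at 5%. The tests of means then agree with two-sided 95% CIs and are held to the same standard as the chi-square tests.

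The cost is one wording change and a modest loss of sensitivity: the difference detectable at 80% power rises by about 13%, or equivalently 80% one-tailed power becomes about 70%. The Results section says that baseline recruitment had not begun as of December 2024, so the change can be made before any data are seen.
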